## Abstract

**Background:**

Type 2 Diabetes (T2D) is common, with a prevalence of approximately 7% of the population in the United Kingdom. The quality of T2D care is inconsistent across the United Kingdom, and Greater Manchester (GM) does not currently achieve the National Institute for Health and Care Excellence treatment targets. Barriers to delivery of care include low attendance and poor engagement with local T2D interventions, which tend to consist of programs of education delivered in traditional, face-to-face clinical settings. Thus, a flexible approach to T2D management that is accessible to people from different backgrounds and communities is needed. Diabetes My Way (DMW) is a digital platform that offers a comprehensive self-management and educational program that should be accessible to a wide range of people through mobile apps and websites. Building on evidence generated by a Scotland-wide pilot study, DMW is being rolled out and tested across GM.

**Objective:**

The overarching objectives are to assess whether DMW improves outcomes for patients with T2D in the GM area, to explore the acceptability of the DMW intervention to stakeholders, and to assess the cost-effectiveness of the intervention.

**Methods:**

A mixed methods approach will be used. We will take a census approach to recruitment in that all eligible participants in GM will be invited to participate. The primary outcomes will be intervention-related changes compared with changes observed in a matched group of controls, and the secondary outcomes will be within-person intervention-related changes. The cost-effectiveness analysis will focus on obtaining reliable estimates of how each intervention affects risk factors such as HbA1c and costs across population groups. Qualitative data will be collected via semistructured interviews and focus groups and organized using template analysis.

**Results:**

As of May 10, 2021, a total of 316 participants have been recruited for the quantitative study and have successfully enrolled. A total of 278 participants attempted to register but did not have appropriate permissions set by the general practitioners to gain access to their data. In total, 10 participants have been recruited for the qualitative study (7 practitioners and 3 patients). An extension to recruitment has been granted for the quantitative element of the research, and analysis should be complete by December 2022. Recruitment and analysis for the qualitative study should be complete by December 2021.

**Conclusions:**

The findings from this study can be used both to develop the DMW system and improve accessibility and usability in more deprived populations generally, thus improving equity in access to support for T2D self-management.

**International Registered Report Identifier (IRRID):**

DERR1-10.2196/26237

## Introduction

### Background

Type 2 diabetes (T2D) is a common long-term condition that affects 7% of the population in the United Kingdom. Compared with people without T2D, those with the condition are at higher risks for a number of complications, including myocardial infarction, stroke, renal replacement therapy, blindness, and major amputation [1,2]. Psychological comorbidities are also common, with depression affecting approximately 1 in 5 adults with T2D and diabetes-related distress affecting approximately 1 in 5 adults with T2D [3]. Self-care (eg, diet, physical activity, and medication adherence) plays a critical role in the management of T2D. Poor self-care can lead to serious diabetes-related complications. Low levels of patient knowledge about T2D contribute to poor glycemic control, and there is evidence in the United Kingdom of major variation in the level of knowledge that people with T2D have about their condition [4].

The management of people with noncommunicable long-term conditions, including T2D, presents a significant challenge to health care systems globally [1]. In the United Kingdom, routine management of T2D is primarily undertaken in primary care settings. There is considerable variation in the quality of diabetes care provided across different services and localities [5]. In Greater Manchester (GM), a mainly urban area in North West England, with a population of 2.8 million people, there are approximately 150,000 adults with T2D. Across GM, there is a poor achievement of national treatment targets for delivering T2D management. Practical and financial challenges exist in delivering interventions aimed at improving T2D knowledge and self-management skills. Current self-management and learning offer in GM is a traditional group-based *structured education* service, and its uptake is low, with attendance rates of approximately 15% [6].

Digital diabetes management systems have the potential to deliver cost-effective self-management support. Diabetes My Way (DMW) is a platform for an open access website (*My Diabetes My Way*) that has been available in Scotland since 2008 to people with diabetes and their carers. Originally, the system included various multimedia resources aimed at improving self-management; from 2010, it offered users access to their clinical data in the form of an electronic personal health record. DMW aims to improve both the outcomes and the experience of people with T2D and provide them with a single care record that is shared with their clinicians. With increased access to and control of their own data, the intention is that patients are able to share decision-making and care planning with clinicians, family, and carers. Through a partner application (MyDiabetesClinical), clinicians can access patient recorded information (with patients’ permission) and provide support for clinical decision-making, care planning, and self-management advice.

By 2020, more than 60,000 people have registered for DMW (including approximately one-third of all people with type 1 diabetes). Evaluations of the system have been encouraging, with 90% of respondents to 1 survey of users reporting that engagement with DMW helped them make better use of their consultation, improved their diabetes management and improved their condition-related knowledge [7]. However, despite positive feedback from users in the Scottish cohort, the overall uptake of DMW was low, with only 5.7% of eligible patients having registered by September 2015, steadily moving to less than 20% in 2020. There was also a disproportionately lower use of DMW among older populations, lower socioeconomic groups, and minority ethnic groups [8].

DMW has evolved based on the evidence base generated from the Scottish pilot and now incorporates an app to be used with mobile devices, which includes tailored *push* decision support, including health warnings and reminders to patients and clinicians. It is this enhanced version of DMW that, as part of the GM Diabetes My Way project, will be offered to all patients with T2D in GM from August 2019 to March 2022. DMW in GM is a collaborative led by the Greater Manchester and Eastern Cheshire Strategic Clinical Networks. Their aim is to provide a more comprehensive self-management and learning offer than is currently available to people with T2D in GM by delivering an enhanced version of DMW across the region. An additional aim is to improve the uptake of the system across all patient groups.

### Integrated Digital Interventions Offered Through the DMW Platform

#### Overview

This work is part of a wider project that aims to test offer a range of other digital supporting services and materials aimed at providing flexible access to support for a wider range of people with T2D. In addition to the DMW platform, this project will offer a range of other digital supporting services and materials through the DMW platform, which will form a package of multiple offerings [9]. The adjunct interventions will include digital support around techniques to change health behaviors (Oviva and Changing Health) and digital support, which aims to assess and improve cognitive functioning (MyCognition).

*Oviva* offers 12-week personalized, frequent, one-to-one care from a diabetes specialist dietician using behavior change techniques [10]. The app or telephone is also used to maintain regular contact with the dietician. The intervention has been evaluated in 204 people with T2D recruited from practices in London. Engagement with the *Oviva* intervention was associated with a 12.8 mmol/mol reduction in hemoglobin A_1c_ (HbA_1c_) level, a 4.3 kg reduction in body weight, and a 24% diabetes remission rate [11]. In our study, we will build on this previous work by increasing the number of participants recruited from an ethnically and socially diverse population.

C*hanging Health* offers a 12-week personalized program consisting of a National Health Services (NHS)-digital-approved and Quality Institute for Self-management Education and Training–accredited app supported by a lifestyle coach trained in behavior change techniques [12]. The educational content on the app consists of short videos, articles, and interactive activities on diet and exercise that participants can view at their convenience on their mobile phone or computer. Upon completion of the educational content, participants can book telephone appointments with their lifestyle coaches at the time of their convenience. All participants will receive 100 minutes of coaching (1×20 minutes introductory call, followed by 8×10-minute calls) across the 12 weeks. The intervention was evaluated in 41 people with T2D recruited from practices in London, and engagement with the *Changing Health* intervention was associated with a 4-mmol/mol reduction in HbA_1c_, a 1.5 kg reduction in body weight, and a 1 mmHg fall in systolic blood pressure [11]. In our study, we will build on this previous work by increasing the number of participants recruited from an ethnically and socially diverse population.

MyCognition is designed to improve cognitive performance, enhance mental resilience, and reduce the impact of stress through cognitive training exercises. The MyCognition intervention can be accessed via a mobile phone or a computer. A web-based assessment tool (taking 15 minutes to complete) provides a personal report on cognitive fitness [13]. A web-based program of personalized educational resources designed to increase cognitive performance follows this. MyCognition also provides access to a personalized game-based training application that can be used for 10-15 minutes per day is also designed to increase cognitive performance. Healthy lifestyle choices are encouraged by the application. Several studies have shown statistically significant improvements in cognitive performance using the application [14-18]. Other interventions designed to improve cognitive performance appear to improve T2D self-management in small studies [18]. In the study we plan to assess the impact of MyCognition on diabetes-related distress in a large cohort of patients with T2D.

#### Acceptability

Acceptability is an important component of the successful implementation of complex interventions. Evaluations of effectiveness can be undermined by the problems of acceptability to stakeholders (patients, carers, and health service staff). If the key protagonists involved encounter barriers to engagement with the components of an intervention, the outcomes can be affected. Assessment of acceptability to participants (patients and staff) is therefore an important part of the DMW GM evaluation that could provide important insights into usability and uptake of the intervention. This is particularly pertinent, given the findings of the study indicating low and divided uptake [7].

Acceptability has been recognized as an important feature of implementation research in the Medical Research Council guidance for the development and evaluation of complex interventions [9]. This guidance recommends that acceptability is explored both in terms of stakeholders’ engagement with the components of an intervention and (for pilot and feasibility studies) with regard to aspects of an associated research study, such as randomization of participants to a control group and completion of outcome measures [19,20] published research into acceptability of complex interventions has increased in number since this guidance was issued. This work has generally focused on barriers and facilitators to engagement [21-23], and *acceptability* has lacked a coherent definition within health services research in terms of its meaning, significance, and theoretical underpinnings. In response, a theoretical framework of acceptability (TFA) has been developed by identifying a relevant and comprehensive theoretical and empirical evidence base. Although this framework is relatively new and has not been widely used and validated, it has been developed from a robust evidence base and offers researchers a useful and unique tool for quantitatively and qualitatively assessing the acceptability of complex interventions [24]. The TFA will be used to inform qualitative data collection and analysis in this study.

### Aims and Objectives

The primary aim is to assess whether digital interventions (DMW and the adjunct interventions) improve T2D self-management across GM using quantitative methods. The primary outcomes will be intervention-related changes compared with changes observed in a matched group of people with T2D not using the interventions (controls), and the secondary outcomes will be within-person intervention-related changes.

The secondary aims are (1) to assess cost-effectiveness in comparison with other services, (2) to assess the acceptability of this package of interventions using qualitative methods, and (3) to perform a process evaluation.

### Specific Objectives

The specific objectives are listed in Textbox 1.

Specific objectives.
**Diabetes My Way–related objectives**
To assess intervention-related changes in hemoglobin A_1c_ (HbA_1c_) levels, systolic blood pressure, cholesterol, smoking, and body weight or BMI (compared with controls and within-person changes).To assess patient uptake (proportion offered intervention who take it up), engagement (time spent on the web and content viewed), user experience (usability, knowledge, and ability to self-manage), retention (proportion of people interacting with the intervention more than once), completion (proportion of people interacting with the intervention who use it within 2 months of the end date (March 31, 2022), and health care use (clinic and hospital attendance and medication use).To assess how Diabetes My Way (DMW) is integrated into care pathways in primary care.

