**Behavioral interventions (Oviva and Changing Health)–related objectives**
To assess average changes in HbA_1c_ levels, systolic blood pressure, cholesterol, smoking, and body weight or BMI in participants using the intervention (compared with controls and within-person changes).To assess patient uptake, engagement, retention, completion, and health care use (defined for DMW above except for completion, which in the case of the behavioral interventions, will be completion of the course).

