#### Duration of Data Access

The University of Manchester will request primary care data on study participants for the period April 1, 2016, to March 30, 2022, through DMW This will enable a 3-year assessment of *baseline* levels of risk factors such as HbA_1c_ and blood pressure before study commencement (July 2019), and up to the end of the intervention (March 31, 2022).

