### Analysis

#### Overview

First, the generalizability and relevance of the intervention in the context of GM will be assessed. We will descriptively compare participants in the interventions to other populations: those who did not participate, the population of GM, and the population of England. For the comparison to those who did not take up the intervention, we will use data on age, sex, ethnicity, residence location socioeconomic deprivation quintile (2019 Index of Multiple Deprivation) and risk factors (from their electronic record) for a comparison with the participants. For the GM and England comparisons, we will compare patients based on age, sex, risk factors, and comorbidities using data sourced from NHS Digital.

Second, we will examine engagement with the intervention (as quantified by relevant metrics in the app, eg, visits and time spent), and descriptively assess how it varies across age groups, sex, ethnic groups (South Asian, Black, mixed, White, and other populations) and socioeconomic deprivation quintiles. A multiple linear regression model will be used to more formally evaluate the association between the variables listed above (age, sex, ethnicity, and socioeconomic deprivation) and engagement.

Third, we will aim to use quasi-experimental methods to evaluate the effectiveness of the intervention on each outcome by comparing prospective changes in outcomes between matched participants and controls and by performing pre- versus postintervention comparisons in participants only. Matching will be performed using the caliper method, which is a modification of the nearest neighbor matching procedure that imposes a tolerance on the difference in cohort characteristics [37]. Here, we will combine calipers relating to age range (+2 or −2 years) and with exact match of gender, ethnicity, and general practice. In the matched group approach, participants receiving the interventions will be randomly matched to nonparticipants on age, sex, ethnicity, and general practice (as a proxy for socioeconomic deprivation).

Where there are differences between participants and controls in relation to matched characteristics or other characteristics such as prevalent cardiovascular disease, we will include these variables as covariates regression models.

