In the presence of time series data, we will use an interrupted time series design for each outcome of interest, which takes into account the preintervention trends of the outcome as well as the information on controls and quantify the effect of the intervention on future outcome levels. If only 2 time points are available (eg, before and after the intervention), we will use a simple linear regression model with clustered errors or a paired 2-tailed *t* test to compare means in each outcome at the 2 time points.

For example, for the main outcome, change in HbA_1c_ levels, we will compare changes from baseline (defined as April 1, 2016, to July 1, 2019) during the intervention period (July 1, 2019, to March 31, 2022) in matched participants and controls after adjusting for clinically significant differences in baseline weight, blood pressure, cholesterol, creatinine, cardiovascular disease, and smoking.

If the numbers of cases and controls are large, we will explore effect heterogeneity in subgroup analyses (as separate models or using interaction terms in the main models described above) by ethnicity, age groups, socioeconomic deprivation quintile, cognitive function (assessed by MyCognition), and level of engagement with digital interventions.

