## Results

As of May 10, 2021, a total of 316 participants have been recruited for the quantitative study and have successfully enrolled. A total of 278 participants attempted to register but did not have appropriate permissions set by the GPs to gain access to their data. A total of 10 participants have been recruited for the qualitative study (7 practitioners and 3 patients). An extension to recruitment has been granted for the quantitative element of the research, and analysis should be complete by June 2022. Recruitment and analysis for the qualitative study should be complete by June 2021.

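### DMW completion is judged in one calendar window despite rolling enrolment, so it depends strongly on enrolment date and cannot be read as sustained use

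*Protocol article*

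**What the plan says.** Textbox 1 (Diabetes My Way–related objectives) defines completion as "completion (proportion of people interacting with the intervention who use it within 2 months of the end date (March 31, 2022". It defines retention as "retention (proportion of people interacting with the intervention more than once". Textbox 3 lists both as secondary outcomes, together with engagement.

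For Oviva and Changing Health, completion is defined differently, "which in the case of the behavioral interventions, will be completion of the course".

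On timing, the Background says that DMW "will be offered to all patients with T2D in GM from August 2019 to March 2022". Duration of Data Access takes the data "up to the end of the intervention (March 31, 2022". Under Enrollment and Informed Consent, each person is enrolled when the web consent is submitted. The Results report 316 enrolled by May 10, 2021, and add: "An extension to recruitment has been granted for the quantitative element of the research". No closing date for recruitment and no minimum time since enrolment are given.

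On engagement, the Analysis Overview offers visits and time spent as examples of the metric, and then says "A multiple linear regression model will be used to more formally evaluate the association" with age, sex, ethnicity and deprivation. The list of possible subgroup analyses ends with "and level of engagement with digital interventions".

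**The concern.** A completion measure for an open-ended platform should say whether people keep using it. Here the end of the window is the same calendar date for everyone, but the start of exposure is not. The required persistence runs from nothing (joined February or March 2022) to about two and a half years (joined August 2019). Two cohorts with identical habits would then show different completion because they joined at different times. Retention cannot fill the gap, because two interactions at any time satisfy it.

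Engagement has a related weakness. If the regression outcome is a cumulative count of visits or total time, it grows with time enrolled, which is not among the named covariates. A group reached later would then look less engaged for that reason alone. Engagement also arises after enrolment and has no counterpart in controls, so a participant-control effect by engagement level selects participants on their later behaviour.

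At stake is the reading of named DMW secondary outcomes: a reader would take the completion figure as evidence of sustained use.

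**Working it through.** The article states no expected completion rate, so there is no figure to reproduce. The check is date arithmetic followed by an illustration.

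**Inputs from the article.** Offer period August 2019 to March 2022, taken as August 1, 2019 to March 31, 2022: 974 days. Window of the last two months, taken as February 1 to March 31, 2022: 59 days. Enrolled by May 10, 2021 (day 649 of the offer period): 316.

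**Step 1: what the rule requires.**
- Joined August 1, 2019: 974 − 59 = 915 days to the window, and 915 / 30.44 = 30.1 months.
- Joined May 10, 2021: about 8.8 months to the window.
- Joined on or after February 1, 2022: 0 months. First use puts the person in numerator and denominator together.

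**Step 2: how many complete automatically.** The window is 59 / 974 = 6.1% of the offer period. If enrolment were uniform (assumption), about 6% would complete by construction. Extrapolating the 316 at a constant rate gives 316 × 974 / 649 = 474 enrolled, of whom 474 × 59 / 974 = about 29 would be automatic.

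**Step 3: illustration.** Assume constant monthly drop-off h with no return after stopping. For a person with u months between enrolment and February 1, 2022, P(complete) = exp(−h·u), and this equals 1 when u = 0. Set 12-month continued use at 50%, so h = −ln(0.5) / 12 = 0.0578 per month.

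- First third (u from 19.4 to 30.1 months, a span of 10.67): [exp(−h × 19.39) − exp(−h × 30.06)] / (h × 10.67) = (0.326 − 0.176) / 0.616 = 24%.
- Uniform: the 915 non-automatic days contribute (1 − 0.176) / 0.0578 = 14.3 months, or about 434 days. Completion is (59 + 434) / 974 = 51%.
- Last third (about 325 days, 59 of them automatic; the other 266 days span 8.73 months): (1 − exp(−h × 8.73)) / h = 6.86 months, or about 209 days. Completion is (59 + 209) / 325 = 82%.

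The same calculation at other assumed levels of 12-month continued use:

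| 12-month use | First third | Uniform | Last third |
|---|---|---|---|
| 20% | 4% | 29% | 66% |
| 50% | 24% | 51% | 82% |
| 80% | 63% | 78% | 94% |

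Across the 50% row, enrolment timing alone moves completion by 82 − 24 = 58 points. Down the uniform column, true continued use moves it by 78 − 29 = 49 points. Both matter, to a similar degree.

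**Step 4: engagement.** A person enrolled on August 1, 2019 can accumulate visits for 974 days. One enrolled on May 10, 2021 has 974 − 649 + 1 = 326 days. At the same visit rate, the totals differ by 974 / 326, about threefold.

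**The case against.** DMW has no course to finish, so activity near the end of the programme is a clear and reproducible service measure. It is descriptive and secondary. The 316 people enrolled by May 2021 would all have to use DMW almost nine months or more after joining, so for them it does carry information. Everyone enrolling in one third of the period is an extreme that the recruitment figures do not show. This stands as a limit on the size of the problem. It does not answer the defect, which follows from the definition whatever the enrolment curve.

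A reader might go further and infer that completion mainly reflects when people enrolled. The documents do not support that. They give neither the enrolment curve nor the drop-off, only about 6% complete automatically under uniform enrolment, and true continued use moves the result about as much as timing does. A reader might also infer that completion will distort the equity comparison. The Analysis Overview attaches comparisons by age, sex, ethnicity and deprivation to engagement, not to completion, and nothing shows that enrolment dates differ between these groups.

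On engagement, the article does not say that raw totals enter the regression. The scale of the outcome is the kind of detail an analysis plan may settle, and no particular model family is required. On subgroups, the analyses are conditional on large numbers, and separate models are allowed, so each engagement stratum could be compared with its own matched controls. It would be wrong to call that analysis impossible. Nor does the point extend to removing cognitive function from the controlled models: the article plans a control group that takes the MyCognition assessment without the intervention. What remains is selection on behaviour after enrolment, which calls for a caution on interpretation.

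**Conclusion.** The concern holds for the DMW completion measure. With one calendar window and rolling enrolment, joiners in the last two months complete by definition, and the persistence asked of the others rises to about 30 months. The proportion therefore depends strongly on enrolment date and should not be read as sustained use. This part rests only on the stated definition and dates, reading the window as the two months up to March 31, 2022.

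The size is illustrative: 24%, 51% or 82% for the same 50% continued use at 12 months, under three assumed enrolment curves, constant drop-off and no return after stopping. The actual value could lie elsewhere.

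The engagement point is conditional: it applies if cumulative visits or time are the outcome. The subgroup point concerns labelling only.

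**What to change.** 1. Redefine DMW completion as any use in a fixed window after each person's own enrolment, among those enrolled at least that long before March 31, 2022. Alternatively, keep the present definition, report it by enrolment cohort, and describe it as activity at programme end.
2. Where the engagement regression uses cumulative visits or time, express them per unit of time enrolled, or adjust for time enrolled.
3. Label the engagement subgroup as exploratory and not causal, because engagement is measured after enrolment and does not exist for controls.

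The cost is small. Website activity is already among the data items, so no new collection should be needed. The downside of the first option is that late enrolees do not count toward completion, which shrinks the denominator, and more so if the extension brings in many people near the end. Reporting by cohort keeps everyone but replaces one figure with several.
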